## Abstract

**Introduction:**

Artificial intelligence (AI) technology has made rapid progress for disease diagnosis and triage. In the field of ophthalmic diseases, image-based diagnosis has achieved high accuracy but still encounters limitations due to the lack of medical history. The emergence of ChatGPT enables human-computer interaction, allowing for the development of a multimodal AI system that integrates interactive text and image information.

**Objective:**

To develop a multimodal AI system using ChatGPT and anterior segment images for diagnosing and triaging ophthalmic diseases. To assess the AI system's performance through a two-stage cross-sectional study, starting with silent evaluation and followed by early clinical evaluation in outpatient clinics.

**Methods and analysis:**

Our study will be conducted across three distinct centers in Shanghai, Nanjing, and Suqian. The development of the smartphone-based multimodal AI system will take place in Shanghai with the goal of achieving ≥90% sensitivity and ≥95% specificity for diagnosing and triaging ophthalmic diseases. The first stage of the cross-sectional study will explore the system's performance in Shanghai's outpatient clinics. Medical histories will be collected without patient interaction, and anterior segment images will be captured using slit lamp equipment. This stage aims for ≥85% sensitivity and ≥95% specificity with a sample size of 100 patients. The second stage will take place at three locations, with Shanghai serving as the internal validation dataset, and Nanjing and Suqian as the external validation dataset. Medical history will be collected through patient interviews, and anterior segment images will be captured via smartphone devices. An expert panel will establish reference standards and assess AI accuracy for diagnosis and triage throughout all stages. A one-vs.-rest strategy will be used for data analysis, and a *post-hoc* power calculation will be performed to evaluate the impact of disease types on AI performance.

**Discussion:**

Our study may provide a user-friendly smartphone-based multimodal AI system for diagnosis and triage of ophthalmic diseases. This innovative system may support early detection of ocular abnormalities, facilitate establishment of a tiered healthcare system, and reduce the burdens on tertiary facilities.

**Trial registration:**

The study was registered in ClinicalTrials.gov on June 25th, 2023 (NCT 05930444).

## Introduction

Artificial intelligence (AI) technology has been generally applied to medical research and practice. Deep learning models, trained on large datasets, have demonstrated impressive capabilities for diagnosis, especially in the fields of image analysis within radiology (van Leeuwen et al., 2021), pathology (Niazi et al., 2019), and dermatology (Phillips et al., 2019). In ophthalmology, AI studies using image data such as fundus images, anterior segment images, optical coherence tomography and computed tomography images have achieved high accuracy in diagnosing glaucoma (Buisson et al., 2021; Akter et al., 2022), age-related macular degeneration (Yan et al., 2021; Chen et al., 2022), diabetic retinopathy (Son et al., 2020; Li et al., 2022), thyroid-associated ophthalmopathy (Shao et al., 2023a), corneal diseases (Gu et al., 2020; Fang et al., 2022; Tiwari et al., 2022), and ocular tumors (Huang et al., 2022; Shao et al., 2023b). Despite these achievements, an obvious limitation of image-based diagnosis is its inability to consider a patient's medical history, which restricts a comprehensive understanding of the patient's condition. To address this limitation, there is a growing need for a multimodal AI system that integrates text and image information to enhance diagnostic performance. Recently, large language models (LLM) have shown great potential in comprehending and reasoning about textual information (Xie et al., 2023). These tools can be utilized in diagnostic AI models to enable textual interaction with patients and obtain in-depth information about the disease to aid in diagnosis.

ChatGPT, a web-application created by OpenAI, utilizes Generative Pre-trained Transformer (GPT) models GPT-3.5 and GPT-4.0, and has brought a new wave to AI research in medicine (Thirunavukarasu et al., 2023). GPT possesses a wide range of knowledge and language capabilities acquired through extensive pre-training on a large scale of text database (Thirunavukarasu et al., 2023). These remarkable human-computer interaction capabilities, exemplified by ChatGPT, allow it to generate natural-language text responses based on user input, indicating the potential application of ChatGPT in online consultations and diagnosis (Ayers et al., 2023). Recently, Gilson et al. (2023) and Kung et al. (2023) reported that ChatGPT possessed sufficient medical knowledge reservoir and reasonable logic loop to pass the United States Medical Licensing Exam (USMLE), highlighting its potential use in medical practice. Berg et al. (2023) generated a ChatGPT-based research and successfully triaged patients at the emergency department. Several studies have also made attempts to utilize ChatGPT for ophthalmic disease diagnosis. For instance, ChatGPT showed good performance in answering ophthalmology board-style questions, indicating its possession of specialized ophthalmic knowledge (Cai et al., 2023). Lyons et al. (2023) compared the triage performance of different AI chatbots in classifying ophthalmic diseases into four urgency categories (self-care, non-urgent, semi-urgent, or urgent), and ChatGPT is reported to be the most prominent one. Rojas-Carabali et al. and Delsoz et al. evaluated the diagnostic accuracy of ChatGPT in uveitis and glaucoma, respectively. Both studies demonstrated promising results for these specific diseases. However, the overall diagnostic accuracy of ChatGPT for various ophthalmic diseases still remains unsatisfactory (Delsoz et al., 2023; Rojas-Carabali et al., 2023).

Although ChatGPT has shown improved diagnostic performance compared to previous natural language models, it still has limitations. This web application is unable to autonomously collect medical history, which therefore restricts its application scenarios and diagnostic accuracy (Howard et al., 2023). In our study, we will implement an innovative dynamic prompt engineering technology and consultation process framework to enable intelligent consultations. This will address the limitation of LLM, which lacks the capability to inquire about patients' primary complaints and symptoms. Moreover, the performance of ChatGPT is unsatisfactory when it comes to questions involving images (Suhag et al., 2023). Recognizing the challenges of low diagnostic accuracy due to the absence of image information in language model consultations, it is necessary to integrate deep learning algorithms for image analysis. This integration allowed our system to effectively handle both text-based consultations and photo image data, leading to significant improvements in the diagnosis of certain ophthalmic diseases.

In our study, we aim to develop a multimodal AI system for the diagnosis and triage of ophthalmic diseases by integrating image analysis with ChatGPT and prompt engineering technology. We will conduct a two-stage cross-sectional study to assess the performance of this multimodal AI system. This innovative multimodal AI system holds the potential for practical real-world applications, such as aiding local communities in the early detection of ocular abnormalities, facilitating the establishment of a tiered healthcare system, and reducing the burden on tertiary healthcare facilities.

## Methods and analysis

### Objectives

Our study consists of a development stage and two evaluation stages of cross-sectional study (Figure 1):

(1) During the *in silico* development stage, we aim to develop a multimodal AI system using ChatGPT and anterior segment images captured in medical facility to facilitate the diagnosis and triage of ophthalmic diseases.(2) During the first evaluation stage (silent evaluation), we aim to evaluate the AI system's performance based on medical histories obtained through observation without patient interaction and anterior segment images captured in medical facility.(3) During the second evaluation stage (early clinical evaluation), we aim to evaluate the AI system's performance in outpatient clinics based on medical histories obtained through patient interview and smartphone-captured anterior segment images.

**Figure 1 F1:**
[figure not shown]
Flowchart of the multimodal AI study.

### Hypotheses

For *in silico* development, our primary goal is to achieve a sensitivity of ≥90% and a specificity of ≥95% for diagnosing ophthalmic diseases. As a secondary outcome, we expect a positive predictive value of ≥90% and a negative predictive value of ≥95% for subspecialty triage of ophthalmic diseases.

For silent evaluation, the primary outcome is to achieve a sensitivity ≥ 85% and specificity ≥ 95% for diagnosing ophthalmic diseases. The secondary outcome is to achieve a positive predictive value ≥ 85% and a negative predictive value ≥ 95% for subspecialty triage of ophthalmic diseases.

For early clinical evaluation, we anticipate the primary outcome to reach a sensitivity ≥ 75% and specificity ≥ 95% for diagnosing ophthalmic diseases. For the secondary outcome, we expect a positive predictive value of ≥80% and a negative predictive value of ≥95% for subspecialty triage of ophthalmic diseases.

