### Sample size calculation

In the *in silico* development stage, the sample size is adjusted based on AI system performance. Initially, each subspecialty involves 20 medical dialogues, with 80% for training ChatGPT and 20% for validation. If ChatGPT cannot generate inquiries, diagnoses, and triage results in the validation dataset, we'll increase the dialogues. Next, 50 virtual cases for the top 1–5 diseases in each subspecialty are input into the diagnostic system. If the sensitivity and specificity of specific diseases do not meet the predefined thresholds (sensitivity ≥ 90%, specificity ≥ 95%), we will proceed to develop a disease-specific image-based diagnostic system. For each disease, we will compile a dataset consisting of 50 cases, including both anterior segment images and their corresponding diagnoses. This dataset will be randomly partitioned into training and testing sets, with the training set supporting system development and the testing set assessing diagnostic accuracy. Should the predetermined criteria (sensitivity ≥ 90%, specificity ≥ 95%) be satisfied, there will be no necessity for further expansion of the sample size.

For the silent evaluation stage, the primary objective is to achieve a sensitivity ≥ 85% and specificity ≥ 95% for diagnosing ophthalmic diseases. To meet this goal, we set sensitivity = 0.85, specificity = 0.95, statistical power (1-β) = 85, significance level (α) = 0.05, and the sample size for each disease is determined to be 22, following the methodology (Tests for One-Sample Sensitivity and Specificity) outlined in Pass15. Since this stage covers at least four different illnesses, we will include a minimum of 88 patients in the entire sample. To account for potential confounding factors, we have opted to include 100 patients in this phase.

For the early clinical evaluation stage, all subjects collected within predefined date ranges at three sites will be included. Data collection at the Shanghai and Nanjing sites spans from July 21 to August 20, 2023. At the Suqian site, data collection is scheduled from August 21 to August 31, 2023.

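### Silent evaluation: the 85% power and 5% alpha quoted for 22 cases per disease do not belong to the stated goal of at least 85% sensitivity

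*Protocol article*

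**What the plan says.** Under Hypotheses, the silent-stage target reads "the primary outcome is to achieve a sensitivity ≥ 85% and specificity ≥ 95" (per cent).

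Under Sample size calculation, the article repeats this target and says the inputs were chosen in order to meet it: "we set sensitivity = 0.85, specificity = 0.95", "statistical power (1-β) = 85" (read here as 85%) and "significance level (α) = 0.05". It names the PASS 15 one-sample procedure for sensitivity and specificity and concludes that "the sample size for each disease is determined to be 22". Four diseases give 88 patients, raised to 100. No null sensitivity, null specificity, prevalence or sidedness is given.

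Under Statistical analysis, the performance measures are to be calculated one-vs.-rest. No test or confidence-bound rule against the marks is described.

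For the early clinical evaluation, Hypotheses says "we anticipate the primary outcome to reach a sensitivity ≥ 75% and specificity ≥ 95" (per cent), and the sample size is simply that "all subjects collected within predefined date ranges at three sites will be included". No alpha, power or number is stated there.

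**The concern.** The value 0.85 has two roles. Under Hypotheses it is the mark to be achieved. In the sample size calculation it is the assumed true sensitivity. A one-sample test planned at 0.85 has its power at 0.85 and its alpha at a lower null value, so a significant result shows that sensitivity exceeds that null. It does not show that sensitivity is at least 85%. The article nevertheless presents the 85% power and 5% alpha as serving the 85% goal.

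A reader would conclude that a system with a true sensitivity of 85% has an 85% chance of meeting the goal, and that a system below 85% has at most a 5% chance. Neither is true. Two different verdicts are also possible on the same data, and a report that a disease meets 85% could rest on a result compatible with a true sensitivity near 65%.

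**Working it through.** **Inputs.** From Sample size calculation: sensitivity 0.85, alpha 0.05, power 85%, n = 22 per disease, 4 × 22 = 88. From Hypotheses: mark of at least 85%. Assumed: the 22 are diseased cases, as the multiplication by four diseases suggests.

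**Step 1. Can 22 be reproduced?** Not from the stated inputs, because the null is missing. It can be reached under assumed nulls. The normal approximation is n = [(z_α·√(p0·q0) + z_β·√(p1·q1)) / (p1 − p0)]². With p1 = 0.85, p0 = 0.56 and two-sided 0.05:

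- numerator: 1.960 × 0.4964 + 1.036 × 0.3571 = 1.343
- divided by 0.29: 4.631
- squared: 21.4, so n = 22

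By the exact one-sided 0.05 test with 22 cases, power at a true 0.85 is:

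| Assumed null | Rejects at | Power |
|---|---|---|
| 0.50 | 16/22 | 0.963 |
| 0.55 | 17/22 | 0.900 |
| 0.60 | 18/22 | 0.774 |
| 0.65 | 19/22 | 0.575 |
| 0.70 | 20/22 | 0.338 |

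If 22 is instead a total, a null of 0.50 needs 13 diseased cases, and at an assumed prevalence of 0.6 that is 13/0.6 = 21.7, again about 22. Either way, 22 fits 0.85 as the alternative against a null of roughly 0.50 to 0.56.

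**Step 2. Could 0.85 be the null?** With 22 cases only 22/22 puts a one-sided 95% lower limit above 0.85 (0.873); the two-sided lower limit at 22/22 is 0.846. For 85% power against a null of 0.85 at one-sided 0.05, the exact test needs 68 diseased cases if the true value is 0.95 and 319 if it is 0.90 (both true values assumed). So 22 is not a sample size for showing that 85% is exceeded.

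**Step 3. What 22 cases give for reaching 85%.** 0.85 × 22 = 18.7, so an observed sensitivity of at least 85% needs 19/22 (86.4%). P(X ≥ 19) for X ~ Binomial(22, p):

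| True sensitivity | Probability |
|---|---|
| 0.70 | 0.068 |
| 0.75 | 0.162 |
| 0.80 | 0.332 |
| 0.85 | 0.575 |
| 0.90 | 0.828 |

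At p = 0.85 the terms are 0.237 + 0.2015 + 0.109 + 0.028 = 0.575. Read as power at 0.85, this is 57.5% and not 85%. Read as error at the 0.85 boundary, it is 57.5% and not 5%. A probability of 85% needs a true sensitivity of about 0.905. The probability falls to 5% only at a true sensitivity of about 0.684.

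**Step 4. What 19/22 shows.** The exact (Clopper-Pearson) two-sided 95% lower limit is 0.651 and the one-sided 95% lower limit is 0.684.

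**Step 5. The specificity mark.** The goal is joint, so the figures in Step 3 are upper bounds. As an illustration, assume 66 non-cases (88 − 22), true specificity 0.95 and independence. At least 95% then needs 63/66, with probability 0.579. The joint probability is 0.575 × 0.579 = 0.33.

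**Step 6. The two verdicts.** With an assumed null of 0.55, 17/22 (77%) or 18/22 (82%) is significant but falls short of 85%.

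**The case against.** The strongest reply is that no section states the decision rule. A reader might infer that the marks are judged on the observed value, because the target is worded as something to achieve and the analysis section lists only measures to be calculated. That remains an inference. The one inferential method named for this stage is a one-sample test, and an analysis plan not shown may add a test or confidence bound. This reply stands, and the missing decision rule is not the point made here. The point needs only what the article itself fixes: 0.85 as goal and as planning value, with power and alpha attached to the goal. A later plan can choose a rule, but it cannot make those figures describe achieving 85%.

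A reader might also extend the criticism to the 75% mark of the early clinical evaluation. The documents do not support that. No alpha, power or sample size is stated for that stage, so nothing is misdescribed, and the mark is already worded as an anticipation.

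A third inference would be that 22 is miscalculated. It cannot be shown to be wrong, since a null near 0.50 to 0.56 reaches it.

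It is also fair to say that nothing in the article makes the next stage depend on the silent-stage result, because the early evaluation starts on fixed dates. This limits the consequence to what is claimed from the stage.

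Finally, the obvious remedy, requiring the lower confidence limit to exceed the null, would not tighten the claim. Under the nulls that fit 22, a one-sided 95% limit is cleared at 16/22 (null 0.50) or 17/22 (null 0.55 or 0.56). At a true 75% this happens with probability 0.70 or 0.52, against 0.16 for 19/22.

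**Conclusion.** The point holds for the silent evaluation only. The stated 85% power and 5% alpha belong to a test against an unnamed lower sensitivity, not to the goal of at least 85%. With 22 diseased cases, the chance of observing at least 85% is 0.575 at a true 85%, about 27 percentage points below the quoted power (85 − 57.5 = 27.5). It is still 0.33 at a true 80% and 0.16 at a true 75%. The probabilities follow from the binomial distribution and rest on reading 22 as diseased cases per disease. The null range of 0.50 to 0.56 is an assumption used only to show what 22 could mean; the mismatch does not depend on it.

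**What to change.** Under Hypotheses and Sample size calculation:

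1. Name the null sensitivity and null specificity used to obtain 22, and the sidedness of the test.
2. Call 85% the expected value, and limit the inferential claim to exceeding the named null, with the exact confidence interval reported for each disease.
3. If at least 85% is kept as the goal, state that 22 cases reach it with probability of about 57% at a true 85%, before the specificity mark, and do not attach 85% power or 5% alpha to it.
4. State that a significant result against the null is not to be reported as meeting 85%.

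This point requires no change to the 75% mark. The cost is wording and a less favourable stated figure. No extra patients are needed.

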### Study design

#### In silico development

Our study will be conducted across three distinct centers located in Shanghai, Nanjing, and Suqian. The development of the multimodal AI system takes place in Shanghai. We will gather medical dialogues (at least 20 dialogues for each subspecialty) from 10 ophthalmic subspecialties, which include general ophthalmology, refractive diseases, strabismus, cornea, cataract, glaucoma, retina, neuro-ophthalmology, oculoplastics and orbital diseases, and ophthalmic emergencies (Supplementary Tables 1, 2). We will utilize these dialogues for prompt engineering to guide the ChatGPT diagnostic system. The brief process is as follows (Figure 2): When users input their chief complaints, the system will categorize them using a chief complaint classifier. Once classified, the system will automatically generate a tailored question list for the user and output each question from the list. After receiving the user's responses, both the chief complaints and all answers will be consolidated into the diagnostic prompt, which ultimately produces the user's diagnosis and triage results. Once the interactive system is developed, virtual cases (at least 50 cases for each disease) representing the top 1–5 diseases in each subspecialty will be introduced to assess diagnostic efficacy. For the diseases that fail to meet the predefined performance thresholds (sensitivity ≥ 90%, specificity ≥ 95%), we will develop an image-based diagnostic system tailored to the cases that have anterior segment images. Subsequently, we will integrate these components to establish a multimodal AI system, with a primary focus on image-based diagnosis, for the comprehensive evaluation of ophthalmic diseases (Figure 3).

**Figure 2 F2:**
[figure not shown]
Flow diagram of the technical details of the multimodal AI system.

**Figure 3 F3:**
[figure not shown]
Overview of the multimodal AI framework and functioning.

#### Silent evaluation

The multimodal AI system will be integrated into a mobile mini-program to enable the diagnosis and triage of ophthalmic diseases. This mini-program will undergo a silent evaluation phase, conducted as a cross-sectional study, in Shanghai (STROBE checklist for cross-sectional study is detailed in Supplementary material 1). A team of researchers will collect medical history on the mobile mini-program in outpatient clinics without intervening in the medical inquiry process. For patients who have undergone anterior segment imaging examinations (Supplementary Table 3), the researchers will provide the corresponding anterior segment images and respond to queries generated by the AI system, utilizing information extracted from the medical dialogues. In cases where no relevant information is available for a specific query, the researcher will denote it as “no information available”.

#### Early clinical evaluation

The mobile mini-program will be upgraded to analyze anterior segment images obtained by smartphone-based devices. An early clinical evaluation of this upgraded program will be simultaneously conducted as a cross-sectional study at three sites: the Eye & ENT Hospital of Fudan University (Shanghai), the Affiliated Eye Hospital of Nanjing Medical University (Nanjing), and Suqian First People's Hospital (Suqian). During the study, researchers will interact with patients to collect necessary information for completing the queries generated by the AI system. Anterior segment images will be captured for each patient by researchers using smartphones (Figure 4). The images should be captured by the macro lens of the smartphone. The positions of both eyes should align with the eye locations specified on the smartphone screen. The images should be large enough to provide a clear view of the affected area of the diseased eye. For all stages, the reference standards of disease diagnoses and subspecialty triage will be determined by an expert panel comprising ophthalmic specialists with a minimum of 5 years of clinical experience. Upon the completion of these data collections, a separate expert panel will assess the accuracy of AI intelligent diagnosis and triage.

**Figure 4 F4:**
[figure not shown]
User interface. Users input their chief complaints in the initial interface. Following this, dialogues between ChatGPT and users are generated once the page transitions. Anterior segment images are obtained after the conversation concludes.

